### Data Management

All hardcopy data will be stored in locked filing cabinets at the participating universities. A document linking participants’ IDs (necessary to match up coach and athlete data at different time points) with participants’ names will be kept securely on a password-protected computer and stored on University secure servers. All data will be kept securely for the number of years stipulated at each participating university (e.g., 7 years at Curtin University), after which they will be destroyed. Data will be entered into a computer spreadsheet by trained research assistants; a subset of that data will be double-checked by members of the research team for accuracy.

### Analyses

The main statistical analyses of the questionnaire data will involve multilevel modeling, accounting for both the longitudinal and nested (athletes within coaches) nature of the data. Country differences will be tested with contrast effects within multilevel modeling. Data from those who dropout from the study will be included in the analyses using intention-to-treat principles. We will compare the results obtained from these analyses with those obtained from a “per protocol analysis” (i.e., excluding participants who dropped out). In terms of missing data, results will be compared using imputation methods and multilevel modeling methods for handling such data. Analysis of the role-playing videos for fidelity assessments will involve repeated-measures MANOVAs. Interviews will be analyzed thematically, within and across countries, by using deductive and inductive approaches to identify patterns in the data (Braun and Clarke, 2006).

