### Hypotheses

•Compared to their baseline levels and to athletes in the control condition, athletes whose coaches complete the training will report: (1) less willingness to take potentially illegal substances (primary outcome), (2) higher perceptions of need supportive and lower perceptions of need thwarting coach motivational strategies (our manipulation check), (3) less favorable attitudes, (4) lower moral disengagement toward doping, (5) higher efficacy to resist doping-related temptations, (6) increased knowledge about anti-doping procedures, and (7) more behaviors to prevent unintentional/inadvertent doping. We also measure self-reported use of performance/recreational substances and drugs, but given that previous studies have found that only 10% of athletes admit to doping use (e.g., Barkoukis et al., 2013; Ntoumanis et al., 2017a), we do not expect to have statistical power to detect significant changes in such use.•The intervention effects on doping-related variables will be mediated via increased psychological need satisfaction/reduced need frustration in the athletes in the experimental condition.•Compared to their baseline levels and to coaches in the control condition, coaches who complete the intervention will (1) utilize more need supportive and less need thwarting communication strategies when discussing doping related issues with their athletes, (2) report higher efficacy to discuss doping with athletes and create an anti-doping atmosphere within the team, (3) rate need supportive communication styles as being more effective (need thwarting style as less effective) in dealing with a doping-related situations, (4) have better knowledge about anti-doping testing procedures, (5) encourage their athletes to use more inadvertent doping prevention behaviors, (6) report stronger anti-doping attitudes, and (7) report lower moral disengagement in doping.•There is insufficient prior evidence to put forward hypotheses regarding any cross-cultural differences in the effectiveness of the intervention.

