#### Participants and Recruitment

We will recruit from sport clubs 20 full-time or part-time coaches in each condition from each country, giving a total sample size of 120 coaches and estimated 1200 athletes. There are no exclusion criteria for coaches based on their own demographic or coach history characteristics. Inclusion criteria include having a minimum of six athletes who are 14 years or older, train at least once a week, and compete on a regular basis. No more than six coaches will be recruited from any given club, and coaches within that club will be allocated to the same condition. Due to the number of recruited participants, we will use a staggered recruitment design. We will aim to recruit from a variety of sports in all three countries, and from both male and female coach and athlete samples. Power estimates have been calculated with the Optimal Design Software (Spybrook et al., 2011) for clustered RCTs with treatment at level 2, primary outcomes at level 1, estimated average number of athletes per coach to be 10, intraclass correlation coefficient of 0.005, small effect size (δ =0.22) for willing to engage in doping, and oversampling by about 30% to counter possible missing values and coach/athlete dropout from the study. Clubs will be assigned randomly to either a control or intervention condition with a 1:1 allocation using permuted blocks of random sizes. The block sizes will not be disclosed to ensure concealment. A researcher will carry out randomization (and allocate clubs to the two arms) via a computer software following recruitment. Allocation concealment will be ensured, as randomization will not be disclosed until after the intervention starts. All research assistants who will collect data will be blind to condition allocation. There will be no circumstances in which unblinding for those individuals will be necessary. Due to the nature of the intervention, participants cannot be blinded to allocation, but they will be strongly encouraged not to discuss the content of their training with coaches from other sport clubs until after the end of the program.

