### Measures

#### Questionnaires

Two questionnaire packs (one for coaches and one for athletes) with the same questions will be administered at all three time-points (with the exception of questions about demographics which will be administered at baseline). Participants will be matched up across time points by a unique ID code given to them by the research team. The questionnaire packs include new questionnaires developed by us for the purposes of this project as well as questionnaires that are already available in the literature; we refer the reader to the original sources for information on the psychometric properties of established questionnaires.

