##### Fidelity assessment

Coaches are also asked to participate in a semi-structured role play. During the role play, a trained research assistant plays the role of an athlete considering taking banned substances while the coach responds in ways which they would consider as a typical response from them. In this hypothetical scenario, a 23-year-old athlete has experienced a performance ‘plateau’ in that they haven’t seen their performance improve over the last 12 months. They are considering taking performance enhancing supplements to break this trend. The role play typically lasts about 20 min and takes place on two occasions, before the intervention and after the end of it, as indicated in **Table 1**. The role plays are audio recorded so that they can be coded later on in terms of the communication style used by the coach. We will use an observational scale (Quested et al., under review) with trained raters, blinded to the experimental condition, to rate the frequency and intensity of need supportive and need-thwarting communication used in these discussions. The aim of this assessment is to establish whether the intervention arm coaches’ communication during the second role play demonstrates fidelity to the intervention (i.e., “treatment enactment”; see Borrelli, 2011), and also to compare the ratings of the coaches in the two arms at each time point. A more rigorous test would have been to code actual communications between coaches and their athletes, however, this was not feasible due to resource constraints as well as the logistical and ethical challenges of filming such discussions. Our role playing is, hence, a proxy measure of fidelity to treatment enactment. We have followed many of Borrelli’s recommendations to enhance fidelity throughout the research process including study design (e.g., explicit use of a theoretical model, pilot testing, and feedback from participants), training (standardized training, accommodate learner differences, assess skill acquisition, and prevent skills drift), treatment delivery (interviews at the end of the project, use of a manual), and treatment receipt (e.g., present material in an engaging way, assess confidence to apply the skills delivered).

### Phase 3

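### The role-play ratings should be compared after the intervention with adjustment for the pre-intervention rating, and the plan should say how baseline enters the questionnaire model

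*Protocol article*

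**What the plan says.** **Role play.** Under Fidelity assessment, each coach does a role play before the intervention and another after it ends, and blinded raters score need-supportive and need-thwarting communication. One aim is to see whether intervention coaches enact the training at the second role play. The other is "also to compare the ratings of the coaches in the two arms at each time point". The Analyses section assigns repeated-measures MANOVAs to these data.

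**Questionnaires.** Coach and athlete packs "with the same questions will be administered at all three time-points": before week 1, in week 13 and 2 months later. The athlete pack contains the primary outcome, willingness to take potentially illegal substances. The main analysis is "multilevel modeling, accounting for both the longitudinal and nested (athletes within coaches) nature of the data", with country contrasts, intention-to-treat and per-protocol analyses, and a comparison of missing-data methods. The article does not say whether baseline is a response or a covariate, whether the arms share a baseline mean, or which contrast is primary. The Hypotheses section reads "Compared to their baseline levels and to athletes in the control condition, athletes whose coaches complete the training will report" less willingness, among other outcomes.

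**Power.** Participants and Recruitment uses "small effect size (δ =0.22) for willing to engage in doping", "intraclass correlation coefficient of 0.005", "estimated average number of athletes per coach to be 10" and about 30% oversampling, "giving a total sample size of 120 coaches and estimated 1200 athletes". It mentions no change score and no baseline covariate.

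**The concern.** Randomised arms have the same expected baseline. If the baseline means are left free and subtracted, sampling noise in the baseline difference is added to the treatment effect. If the follow-up scores are compared without using baseline, the variation that baseline explains stays in the error term. Adjusting for baseline avoids both losses and uses only data already collected.

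For the role play this follows from what the article states. With two occasions, the arm-by-time test of a repeated-measures MANOVA is a test of difference in change. A comparison at each time point is unadjusted, and at the first occasion it tests a difference that can only be due to chance. The trial plans for at most 120 coaches, so precision at coach level matters.

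For the questionnaire scales the same loss would occur only if the longitudinal model is fitted with free baseline means and read through the arm-by-time contrast. The article leaves this open.

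**Working it through.** **Inputs from the article:** 120 coaches, 10 athletes per coach, ICC 0.005, standardised effect 0.22, oversampling about 30%, 1:1 allocation. The coach-training effect d = 0.63 is the meta-analytic figure cited in the Introduction.

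**Assumptions:** two-sided 5%; 90% power for reproducing the sample size (the article states neither); correlation rho between baseline and follow-up of 0.3 to 0.7, the same at athlete and coach level; equal variances on the occasions compared.

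**1. The plan's own figure.** 435 athletes per arm are needed for an effect of 0.22 at 90% power. The design effect is 1 + 9 × 0.005 = 1.045. Then 2 × 435 × 1.045 = 909 athletes, or 91 coaches; × 1.3 = 118 coaches. This is within 3% of 120 and fits a comparison of one follow-up score without baseline. Removing the oversampling gives 120/1.3 = 92 coaches.

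**2. Variance factors**, relative to an unadjusted follow-up comparison (= 1):
- difference in change, free baseline means: 2(1 − rho)
- adjusted for baseline: 1 − rho²
- ratio of adjusted to change: (1 − rho²) / [2(1 − rho)] = (1 + rho)/2

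| rho | change | adjusted | cut against change | cut against unadjusted |
|---|---|---|---|---|
| 0.3 | 1.40 | 0.91 | 35% | 9% |
| 0.5 | 1.00 | 0.75 | 25% | 25% |
| 0.7 | 0.60 | 0.51 | 15% | 49% |

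**3. Common baseline mean.** By generalised least squares with baseline and one follow-up as responses and one person per arm, a shared baseline mean gives a treatment-effect variance of 1.82, 1.50 and 1.02 at rho = 0.3, 0.5 and 0.7. This equals 2(1 − rho²), the same as covariate adjustment. Free baseline means with a change contrast give 2.80, 2.00 and 1.20, which equals 4(1 − rho).

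**4. Role play, illustration only.** SE = √(4v/J), where J is the number of coaches and v the variance factor; noncentral t with J − 2 degrees of freedom; d = 0.63; clustering of coaches in clubs ignored. At rho = 0.5, where change and unadjusted contrasts coincide, J = 92 gives an SE of 0.209 falling to 0.181 and power rising from 84.8% to 93.2%. With J = 84 (120 × 0.7), power rises from 81.4% to 90.9%.

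**5. Willingness, if a free-baseline change contrast were used.** SE = √{4[0.005 + 0.995/10]v/J}, J = 92, effect 0.22:

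| rho | power, change | power, adjusted | gain (points) |
|---|---|---|---|
| 0.3 | 77.9% | 92.3% | 14 |
| 0.5 | 89.8% | 96.1% | 6 |
| 0.7 | 98.6% | 99.5% | 1 |

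If all 120 coaches and 1200 athletes are kept, power at rho = 0.5 rises from 95.9% to about 99%, 3 points.

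**The case against.** A reader might infer that baseline willingness enters the main model only as another repeated response with a change-from-baseline contrast, so that the plan throws away precision on the primary outcome. The documents do not support this. The Analyses sentence names no contrast and no role for baseline, and the Hypotheses section states an expectation, not an estimator. A longitudinal model with a common baseline mean would satisfy the sentence and lose nothing (step 3). A condensed article may also leave such terms to a full protocol or analysis plan that is not shown. This objection stands, so for the questionnaires the point is only an improvement to specify.

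The size is also uncertain. Rho is not given, and against the unadjusted comparison implied by the sample size, a change contrast does worse only when rho is below 0.5. Nor do the documents support a claim that chance baseline imbalance is likely because clubs are randomised: at an ICC of 0.005 the design effect is only 1.045, and no club-level figure is given.

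For the role play it can be said that this is a proxy fidelity measure, that a repeated-measures analysis does use the pre-intervention rating through the arm-by-time term, and that d = 0.63 describes such training programmes in general, not these ratings. All three are fair. They limit the importance and the power illustration, but using the earlier rating by subtraction is still less precise than adjusting for it at any rho below 1.

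**Conclusion.** The point holds for the role play. The stated analysis is a difference in change or an unadjusted comparison, and a more precise analysis is available from the same data. The variance of each rating's contrast falls by 15% to 35% against change for rho from 0.7 to 0.3, and by 25% at rho = 0.5. These percentages rest on the assumed rho and on equal variances on the two occasions; the power figures rest in addition on a borrowed effect size and on ignoring clubs.

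For willingness and the other questionnaire scales there is no demonstrated error. The article leaves the role of baseline open, and fixing it is a free improvement. Its value against a free-baseline change contrast ranges from about 14 power points at rho = 0.3 to 1 at rho = 0.7 with 92 coaches, and it is nil if the full plan already constrains or adjusts for baseline.

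**What to change.** **Role play.** Replace the repeated-measures MANOVAs and the comparison at each time point with a between-arm comparison of the post-intervention ratings adjusted for the pre-intervention ratings (ANCOVA per rating, or MANCOVA jointly). Drop the between-arm test at baseline and report baseline ratings by arm descriptively. The enactment aim within the intervention arm can stay as a descriptive summary.

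**Questionnaires.** Add one sentence to Analyses. Either all three time points are responses in the multilevel model with a common baseline mean across arms, and the treatment effects are the arm differences at week 13 and at 2 months; or the two follow-ups are responses with the participant's own baseline score as covariate. Apply the same rule to every athlete and coach scale measured at baseline with the same questions.

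**Cost.** A few sentences, with no new data, visits or participants. Athletes or coaches without a baseline score need the common-baseline form or simple baseline imputation to stay in the intention-to-treat analysis.

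### Clubs are randomised but the stated nesting stops at coaches, so type I error can exceed the nominal level where clubs supply several coaches and between-club variance enters the contrast tested

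*Protocol article*

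**What the plan says.** Under Participants and Recruitment, the protocol article makes the club the unit of allocation: "Clubs will be assigned randomly to either a control or intervention condition with a 1:1 allocation using permuted blocks of random sizes". It expects clubs with several coaches and fixes how they are handled: "No more than six coaches will be recruited from any given club, and coaches within that club will be allocated to the same condition".

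The power calculation in the same section is two-level, with "treatment at level 2, primary outcomes at level 1" and "estimated average number of athletes per coach to be 10". Its cluster is therefore the coach. Its other inputs are an "intraclass correlation coefficient of 0.005", a standardised effect of 0.22 and about 30% oversampling. The target is 120 coaches and about 1200 athletes.

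The Analyses section states the main model for the questionnaire data as "multilevel modeling, accounting for both the longitudinal and nested (athletes within coaches) nature of the data". Nothing in the article adds a club random effect, club-robust standard errors or an analysis at club level. The limitations paragraph in Phase 3 names organisational pressures at club level among the influences on athletes' doping tendencies and says that they are not assessed.

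**The concern.** In a cluster randomised trial, the uncertainty of the arm effect is set by how much the randomised units differ. Here that unit is the club. A model whose top level is the coach treats up to six coaches of one club, or about 60 athletes at 10 per coach, as separately assigned. Any positive correlation between those coaches on the tested contrast is then missing from the standard error.

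The error runs one way: intervals too narrow and too many false positives. At stake are the primary superiority test on willingness to take potentially illegal substances and the secondary athlete outcomes. The seven coach hypotheses and the repeated-measures MANOVAs on the role plays are also exposed, because coaches from one club would count as independent there too.

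This is not a detail left to an analysis plan. The article names the hierarchy, and the one it names does not match its own randomisation.

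**Working it through.** **Inputs from the article.** Athletes per coach 10; intraclass correlation 0.005; effect 0.22 SD; oversampling about 30%; 120 coaches (60 per arm); coaches per club k between 1 and 6.

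**Assumed, because not stated.** Two-sided 5% level; 90% power; equal clubs; the split of variance between club and coach.

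**1. The plan's sample size, with the coach as cluster.**
- Per arm without clustering: 2 × (1.960 + 1.282)² / 0.22² = 434.2, so 435.
- Design effect: 1 + (10 − 1) × 0.005 = 1.045.
- Total: 2 × 435 × 1.045 = 909 athletes; × 1.3 = 1182 athletes, or 118 coaches.

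This is within 3% of 1200 and 120, so the calculation can be reproduced with no club level in it. At 80% power the same steps give 883 athletes, which does not match.

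**2. Post-intervention comparison with club ignored.** Set the total variance to 1, with club part c, coach part h and remainder 1 − c − h.
- Variance of a coach mean: v = c + h + (1 − c − h)/10.
- Correlation between coaches of one club: r = c/v.
- True variance over model variance: R = 1 + (k − 1)r.
- True level: 2 × [1 − Φ(1.96/√R)].

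With 0.005 wholly between clubs (c = 0.005, h = 0), v = 0.005 + 0.0995 = 0.1045 and r = 0.0478.

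| Coaches per club | R | True level, formula | True level, simulated |
|---|---|---|---|
| 1 | 1.000 | 5.00% | 5.1% |
| 2 | 1.048 | 5.55% | 5.5% |
| 3 | 1.096 | 6.11% | 6.0% |
| 6 | 1.239 | 7.83% | 7.8% |

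The simulation used 40,000 null trials per row. With 0.005 split evenly between club and coach, it gave 5.2%, 5.7% and 6.7% for 2, 3 and 6 coaches per club. Testing club means instead gave 4.8% to 5.3% in every setting tried.

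**3. Higher club correlations (assumed, not from the article).** With c = 0.02 and h = 0.005, r = 0.163 and the formula gives 8.9% (k = 3) and 14.6% (k = 6). With c = 0.05 and h = 0.005, r = 0.334 and it gives 12.9% and 23.1%.

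**4. Change from baseline.** A stable club effect is in both measurements and cancels. Suppose a share f of the club variance is club-by-time, independent at each occasion, and half of the remainder is stable athlete variance.
- Club part of the change: 2fc.
- Remainder of a coach's mean change: 2 × 0.5 × (1 − c − h)/10 = (1 − c − h)/10.
- Correlation: r = 2fc / [2fc + (1 − c − h)/10].

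With f = 0, r = 0 and the level is 5% for every k and c. With f = 0.2 (assumed) and c = 0.005, h = 0, r = 0.002/0.1015 = 0.0197. The level is then 5.2%, 5.5% and 6.2% for k = 2, 3 and 6. With f = 0.2, c = 0.05, h = 0.005 and k = 6, r = 0.02/0.1145 = 0.175 and the level is 15.2%, against 23.1% for the post-intervention comparison.

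**The case against.** The strongest objection is that the planned analysis is longitudinal. The Hypotheses section compares athletes with their own baseline as well as with controls, and outcomes are taken at baseline, week 13 and two months later. If the arm effect is read from an arm-by-time contrast, stable differences between clubs drop out and the post-intervention figures do not apply. That stands: inflation then needs club-by-time variance, and a random club intercept alone would not repair it.

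The magnitude is also uncertain. Six coaches is a cap, not an average; all clubs at six would mean 120 coaches from only 20 clubs. In a two-level calculation, 0.005 already contains any club variance, so placing all of it between clubs is the extreme case. These points stand as well.

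A reader might infer that type I error certainly exceeds 5%, or that it reaches 15% to 23%. The article supports neither. The first depends on multi-coach clubs and on club variance in the tested contrast. The second needs club correlations 4 to 10 times the protocol's own value, with every club at the cap. Nor does the article state a degrees-of-freedom method, so it cannot be said that degrees of freedom will be counted on coaches.

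It can be added that an analysis plan not shown may specify more. That does not remove the mismatch. The article states a nesting that leaves out the randomised unit, and its power calculation has the same structure, so the clause is hard to read as loose shorthand.

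**Conclusion.** The mismatch holds: clubs are randomised, and the stated main analysis stops at coaches. The consequence is conditional. Standard errors are too small, and the type I error exceeds its nominal level, if clubs contribute more than one coach and there is between-club variance in the contrast tested. That means stable club variance for a post-intervention comparison, and club-by-time variance for a change or arm-by-time contrast.

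On the protocol's own 0.005, placed wholly at club level, the excess for a post-intervention comparison is modest: about 5.5% to 7.8% for two to six coaches per club. It is larger only under assumed higher club correlations, smaller for a change contrast (none without club-by-time variance), and absent with one coach per club. The six-coach cap and the same-arm rule show that multi-coach clubs were expected. Because the number of clubs, the coaches per club and a club correlation are not stated, the exact size cannot be fixed.

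**What to change.** In the Analyses section, replace the nesting clause so that it reads: repeated measures within athletes, athletes within coaches, and coaches within clubs, with a random intercept for club and a random club-by-time effect. Club-clustered robust standard errors are an acceptable alternative. Test the arm effect with a small-sample correction based on the number of clubs, such as Kenward-Roger for the mixed model. Apply club clustering to the coach-level outcomes and the role-play analysis too. Re-check power with clubs as clusters once the number of clubs and the coaches per club are known.

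The cost is small. Club membership is already on record because it drives allocation, and recruitment was still under way in two of the three countries. The price is somewhat wider intervals and a slightly more complex model.
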